### Statistical analysis

2.11

Data will be processed and analyzed with R 4.4.2 [66] or newer and the RStudio interface [67].

First, to test proximal and trajectory effects with and without photography, as well as the moderating role of quality of practice (Objectives 1.a, 1.b, 2, and 3), linear mixed-effects models will be fitted using the *lmerTest* package [68]. Separate models will be fitted for each proximal outcome within each microintervention as the dependent variables. For the 50th birthday party microintervention, participants from the RWM and CWM conditions will be pooled for the pre-post analysis, as the photography component in the CWM condition is introduced only after the post-microintervention EMA. Thus, time (pre- vs. post-microintervention), quality of practice, and their interaction will be entered as fixed-effect predictors. For values awareness, frequency of valued actions and awareness during valued actions, which require time and opportunity to occur or be noticed in daily life, change will be examined using the next available EMA assessment, collected the following day before the 3-min wake-up microintervention. Given that this assessment occurs after the photography task, models including condition will be conducted to examine potential RWM-CWM differences. For the 3-min wake-up microintervention, condition (RWM, CWM), time (pre- vs. post-microintervention), day (from 1 to 6), quality of practice, and their interactions will be entered as fixed-effect predictors. For the friendly reminder microintervention, condition (RWM, CWM, control), time (pre- vs. post-microintervention), day (from 1 to 6), quality of practice, and their interactions will be entered as fixed-effect predictors. Additionally, to examine the combined effect of the 3-min wake-up and friendly reminder microinterventions across the intervention period, linear mixed-effects models will be fitted using the variables assessed in the first EMA assessment of each day as dependent variables. This approach will allow us to examine whether values awareness, frequency of valued actions and awareness during valued actions change across repeated daily engagement with the intervention. Condition (RWM, CWM, control), day (from 1 to 6), and their interaction will be entered as fixed-effect predictors. Participant will be entered as a random-effect predictor in all models. Models will be estimated using restricted maximum likelihood (REML). Under the missing at random (MAR) assumption, all available data will be used, so participants with incomplete EMA data will still contribute to the analyses based on the observations they provide.

Second, to test the distal effects with and without photography on mental health and values-related outcomes (Objectives 1.c and 2), two-way mixed ANOVAs will be conducted with condition (RWM, CWM, control) as the between-subject factor and time (baseline, post-intervention, and two-week follow-up) as the within-subject factor. The inclusion of the MIA as a covariate will be performed if the assumptions for ANCOVA are met (objective 3).

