### Control group

2.6

Participants in the control group will not receive any of the microinterventions and will only be assessed daily with the EMA pre-questions, in addition to the assessments at time points 1 (baseline), 2 (post), and 3 (follow-up). After the follow-up, participants in the control condition will receive an email offering them the opportunity to randomly receive one of the two interventions.

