**Fig. 2 fig2:**
[figure not shown]
Schedule of microinterventions. Abbreviations: FR: Friendly reminder

The 50th birthday party microintervention will be sent on the first day after downloading the app, and it will be sent only once with the following message: “It's time to start the journey! Listen to your first visualization”*.* When participants enter the app, this module will be named “Starting your journey!” and will remain available for the next 24 h. Throughout the day, participants will receive two reminders if the strategy has not been completed. The first reminder will be sent at 3:00 p.m. with the message: “Don't forget your first notification! It's really important to us that you complete it”. The second reminder will be sent at 9:00 p.m. with the message: “To stay in the study, please complete today's notification. We'd love to keep you on board!”

The 3-min wake-up microintervention will be sent daily in the morning during the 6 days following the initial microintervention, with the message: “Time for a quick exercise! It will disappear at 12:00 p.m.” When participants enter the app, this module will be named “Before starting your day!” and will be available from 6:00 a.m. to 12:00 p.m. Reminders will be sent at 9:00 a.m. and at 11:00 a.m. with the following messages, respectively: “Don't miss your morning check-in! It takes less than 5 min – Available until 12:00!” and “Don't forget about me! Morning notification disappears in 1 h”

The friendly reminder microintervention will be sent three times per day and will be available from 3:00 p.m. to 5:00 p.m., from 6:00 p.m. to 8:00 p.m., and from 9:00 p.m. to 11:00 p.m., on the same days as the morning notifications They will appear with the message: “Just 1 question”.

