#### Quality of values practice

2.10.3

The quality of values practice will be measured after the 50th birthday party with the Values Practice Quality Scale (VPQS). Considering that compassion and values-based practices share common elements, such as the use of imagery and bodily sensations, we adapted the Compassion Practice Quality Scale (CPQS) by Navarrete et al. [42] and constructed the VPQS, particularly for this study. The adapted VPQS was based on values literature and incorporates expressions specifically aligned with the values process, ensuring greater relevance and applicability. This 10-item scale measures the values practice quality with two subscales: imagery (items 1,2,3,4,6, and 8), e.g., “During the exercise, I had a lot of difficulty choosing the elements that made up the mental scene) and somatic (items 5,7,9, and 10) e.g., “During the exercise, I noticed feelings of vitality and expansion in my body”. Items are rated on a scale from 0 to 100, indicating the percentage of time their experience aligns with each statement. Higher scores indicate better practice quality (fewer difficulties), except for negative items (items 1, 2, 3, 4, 6, and 8). CPQS has good reliability and validity in its version in Spanish [42]. Reliability and validity of the VPQS remains to be tested. A short 4-item daily questionnaire for assessing the quality of values practice after the 3-min wake-up will be created by selecting the items with the highest factor loadings from the original scale.

Table 2 provides an overview of the proximal outcomes.

**Table 2 tbl2:** Study variables, EMA items and assessment time points.

Variable	EMA items	50th birthday party		3-min wake-up		Friendly reminder
		Pre	Post	Pre	Post	Pre
Well-being	At this moment, what is your level of well-being?	x	x	x	x	-
	How happy do you feel right now?	x	x	x	x	-
	At this moment, to what extent are you satisfied with your life?	x	x	x	x	-
	At this moment, to what extent are you feeling that your life has a sense of direction or meaning to it?	x	x	x	x	-
Depression	At this moment, to what extent are you feeling little interest or pleasure in doing things?	x	x	x	x	-
	At this moment, to what extent are you feeling down, depressed or hopeless?	x	x	x	x	-
Anxiety	At this moment, to what extent are you feeling nervous, anxious, or on edge?	x	x	x	x	-
	At this moment, to what extent are you not being able to stop or control worrying?	x	x	x	x	-

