Values clarity	At this moment, how easy is it for you to identify the values that drive your life?	x	x	x	x	-
Values awareness	In the last 24 h, to what extent have you been consciously aware of your values?/Since the last notification, to what extent have you been aware of your values? (for friendly reminders notifications)	x	-	x	-	x
Frequency of valued actions	In the last 24 h, how many of your actions have been aligned with your values?	x	-	x	-	-
Awareness during valued actions	And how aware were you, while doing them, that you were acting according to your values?	x	-	x	-	-
Intention to engage in valued actions	To what extent do you INTEND to take actions aligned with your values in the following hours?	x	x	x	x	-
Quality of values practice	1. During the practice, I had great difficulty choosing the elements that shaped up the mental scene that I was using to clarify my values.	-	x	-	-	-
	2. During the practice, I had many difficulties constructing the mental scene that I was using to connect with my values.	-	x	-	x	-
	3. During the practice, I had great difficulty holding the mental scene that I was using to clarify my values.	-	x	-	-	-
	4. During the practice, I had a hard time manipulating the mental scene that I was using to connect with my values.	-	x	-	x	-
	5. During the practice, I managed to generate a sense of meaning and significance towards my life.	-	x	-	x	-
	6. During the practice, I had great difficulty seeing clearly and in detail the mental scene that I was using to clarify my values.	-	x	-	-	-
	7. During the practice, I felt that I was completely within the visualization, forgetting that I was in this room.	-	x	-	-	-
	8. During the practice, I self-criticized myself for not being able to clarify my values.	-	x	-	-	-
	9. During the practice, I noticed a sense of vitality or expansion in my body.	-	x	-	x	-
	10. During the practice, I perceived a great connection and sense of closeness with the mental scene that I was using to clarify my values.	-	x	-	-	-

*Note*. Pre = pre-microintervention; Post = post-microintervention.

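### The friendly-reminder model cannot be estimated as specified: reminders have one pre assessment and no practice-quality rating, and controls never have one

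*Protocol article*

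**What the plan says.** Section 2.11 sets the general rule: "Separate models will be fitted for each proximal outcome within each microintervention as the dependent variables". It then names the reminder model: "For the friendly reminder microintervention, condition (RWM, CWM, control), time (pre- vs. post-microintervention), day (from 1 to 6), quality of practice, and their interactions", entered as fixed effects, with a random effect for participant.

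The data for that model are fixed elsewhere in the protocol:

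- **Reminder content.** Table 2 has one reminder column, headed Pre. One item is marked there: "Since the last notification, to what extent have you been aware of your values? (for friendly reminders notifications"). Section 2.7 agrees, since the notification announces a single question. It is sent three times a day on the same six days as the wake-up.
- **Practice quality.** Section 2.10.3 places the full scale after the first exercise: "The quality of values practice will be measured after the 50th birthday party with the Values Practice Quality Scale (VPQS"). It adds a short form: "A short 4-item daily questionnaire for assessing the quality of values practice after the 3-min wake-up will be created". In Table 2 all ten items are blank at the reminder.
- **Control arm.** Section 2.6: "Participants in the control group will not receive any of the microinterventions and will only be assessed daily with the EMA pre-questions", besides the three distal assessments.

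Step 2 of section 2.8 speaks of EMA questions on both sides of every exercise, which does not match the reminder column of Table 2.

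**The concern.** The model needs four factors: condition, time, day and practice quality. The schedule supplies condition and day. It gives no post value at a reminder, no practice-quality rating at a reminder, and no practice-quality rating of any kind in the control arm.

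This is the only reminder-specific model, and the only model in section 2.11 for a single microintervention that includes the randomised control arm. An analyst following the text must improvise: choose what counts as post, choose which rating stands in for practice quality, and decide whether controls stay. Mixed-model software will not necessarily stop. It may reject a one-level factor, or it may delete incomplete rows and drop aliased terms. In the second case a three-arm test becomes a two-arm test without anyone having decided so.

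**Working it through.** The protocol gives no figure for this model, so the check is one of estimability: count the fixed-effect columns that the formula asks for and the number that the schedule can identify.

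**Inputs**
- Arms: 3. Total sample 159 (section 2.2), 1:1:1 allocation, so 159 / 3 = 53 per arm.
- Prompts: 3 reminders a day × 6 days = 18 per participant (section 2.7).
- Records at full compliance: 159 × 18 = 2,862, of which control 53 × 18 = 954 and RWM plus CWM 1,908. This assumes that controls get all 18 prompts; section 2.6 says only that they are assessed daily.
- Day entered as a linear term (assumption).

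**Columns requested.** Condition (3) × time (2) × day (intercept and slope, 2) × practice quality (intercept and slope, 2) = 24.

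**What the schedule identifies**

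| Reading | Usable records | Columns | Rank |
|---|---|---|---|
| Literal: rating needed at the reminder | 0 in any arm | 24 | none |
| Pre only; morning wake-up rating carried forward in RWM and CWM | 1,908 | 24 | 8 |
| As above, with post = next notification | control all lost | 24 | 16 |
| As above, with control quality set to 0 | control kept | 24 | 20 |

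The ranks follow by counting:
- Row 2: 2 arms × 1 time level × 2 × 2 = 8.
- Row 3: 2 × 2 × 2 × 2 = 16.
- Row 4: those 16 plus 4 for control (time 2 × day 2) = 20. Control has no variation in quality, so its four quality terms stay inestimable, and the value 0 is arbitrary.

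Each was confirmed by computing the rank of a design matrix built to the Table 2 schedule.

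**Alternatives that work**
- Condition × day, three arms, no time, no quality: 3 × 2 = 6 columns, rank 6.
- Condition × time × day, three arms, post = next notification, no quality: 3 × 2 × 2 = 12 columns, rank 12.
- Condition × time × day × quality in RWM and CWM only, post = next notification, morning rating: 16 columns, rank 16.

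Practice quality is therefore the term that removes the control arm. The time factor is a separate fault and can be repaired by a definition.

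**The case against.** **Post may mean the next notification.** The item asks about the time since the last notification, so a later answer does cover the period after an earlier reminder. Section 2.11 also uses a next-assessment rule for outcomes that need time to show. It states that rule only for the 50th birthday party, tied to the following morning's assessment. A reader might infer that the time factor is necessarily empty. That is too strong: it is undefined for reminders, and an explicit definition makes it estimable. This part of the objection stands, but it does not bring the controls back while quality is in the model.

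**The analysis plan will settle it.** Leaving detail to a later document would be no fault. Here the protocol names predictors that its own schedule cannot supply.

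**Missing data are handled under MAR.** Control practice quality is not a missing value; it does not exist, because controls do no practice. A likelihood fit does not fill in an absent covariate. It drops the row.

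**Other analyses cover the reminder.** A reader might infer that Hypotheses 1 to 3 have no workable analysis for this microintervention. The document does not support that. Section 2.11 also specifies condition × day on the first EMA of each day, for the combined effect of wake-up and reminder. That model has neither time nor quality and keeps all three arms. The distal ANOVAs are likewise intact, and section 2.2 attaches the main analysis to that design. What is lost is the reminder-specific effect on one item and its moderation, which section 1.5 describes as exploratory.

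**The size of the loss.** A loss of one third of the records (954 of 2,862) might be read as the literal consequence. It applies only after morning ratings are carried forward. Read literally, every reminder record lacks a rating.

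**Conclusion.** The point holds. The reminder model in section 2.11 cannot be estimated as specified, because Table 2 and sections 2.6 and 2.10.3 do not provide the post value or the practice-quality rating that it requires. No reading that leaves practice quality in the model recovers its control-arm terms. The most generous reading without invented control values identifies 16 of 24 columns and loses the whole control arm.

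The damage is confined to one model with one outcome item. The record counts rest on 53 per arm, full compliance and 18 prompts in every arm; the ranks rest on day as a linear term. The loss of the control arm depends on none of these.

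**What to change.** Amend the reminder paragraph of section 2.11:

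1. **Main reminder model.** Values awareness at each reminder on condition (RWM, CWM, control) × day, participant random, all three arms, no practice quality.
2. **Time.** Either drop it, or define post as the answer at the next notification. If it is defined, say what follows the last reminder of a day: the next assessment is the morning one, where Table 2 uses a 24-hour recall wording.
3. **Practice quality.** Test it in a separate model in RWM and CWM only, and state that the rating is that morning's wake-up short form, so it does not rate the reminder itself.
4. **Optional occasion term.** A term for first, second or third reminder of the day may be added. The change from the first to the later two should not be presented as a pure reminder effect: it is mixed with fading of the morning wake-up effect, with different recall periods, and with carry-over from earlier days' reminders.
5. **Consistency.** Reconcile step 2 of section 2.8 with the reminder column of Table 2.

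The cost is wording, settled before the analysis. No new data are needed.

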Thus, MIA and somatosensory engagement may provide a useful starting point for investigating the quality of values practice. Understanding these internal dimensions is crucial for clarifying the mechanisms through which VBIs achieve their effects. When values practice is supported by stronger mental imagery and somatosensory engagement, individuals may experience a deeper connection with their values and, consequently, greater valued living. This deeper valued living, in turn, is expected to amplify positive effects across dimensions of sustainable mental health. However, few studies have examined the role of practice quality in values-focused work.

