### Objectives and hypothesis

1.5

Based on the literature reviewed above, this study aims to:(1)Examine the effects of three mobile phone-based microinterventions targeting valued living on mental health and values-related outcomes over one week. Specifically, we aim to investigate effects at three temporal levels: (1.a) proximal effects (immediate changes following each microintervention), (1.b) trajectory effects (changes across days associated with repeated microintervention use), and (1.c) distal effects (changes observed after the intervention period and at the two-week follow-up).(2)Examine whether photography-supported microinterventions enhance the effects referred to in the first objective compared to non-photography-supported microinterventions.(3)Explore the moderating role of baseline MIA and momentary quality of values practice on the effects of the microinterventions.

We formulate the following hypotheses:Hypothesis 1The three values-based microinterventions will show positive effects on mental health and values-related outcomes across the three temporal levels: (i.e., proximal, trajectory and distal effects).Hypothesis 2Photography-supported microinterventions will enhance the effects referred to in Hypothesis 1 compared to non-photography-supported microinterventions across all three temporal levels.Hypothesis 3Higher baseline MIA and higher quality of values practice will be associated with stronger microintervention effects referred to in Hypothesis 1 across the three temporal levels.

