## Discussion

4

This study presents the protocol for a three-arm randomized controlled trial designed to evaluate the effects of three mobile phone-based microinterventions targeting valued living on mental health and values-related outcomes in university students. In addition, the study will examine whether adding a photography component enhances intervention effects and whether quality of practice moderates proximal and trajectory effects.

This study may contribute to the literature at several levels. Theoretically, the study may inform the literature on positive psychological interventions (PPIs). Although values-focused work has been primarily developed within ACT, where values are understood as a key process for promoting psychological flexibility, it also aligns with positive psychology's emphasis on cultivating adaptive psychological resources that support well-being [69]. Following the model of sustainable mental health [9], valued living may also represent a complementary resource-oriented pathway for supporting adaptation, well-being, and mental health over time.

Conceptually, the study approaches valued living as a multidimensional process. This perspective extends traditional approaches that often conceptualize valued living as a unitary construct, allowing for a more fine-grained understanding of which values-related processes are most responsive to intervention and most strongly associated with well-being and mental health.

Regarding the intervention, the study evaluates values-based microinterventions as brief, targeted strategies designed to isolate and examine the specific effects of values work. This is relevant because values-related processes have often been embedded within broader multicomponent interventions, making it difficult to determine their unique contribution to mental health outcomes. The study also compares different values-oriented exercises, including strategies grounded in existing literature (i.e., 50th birthday party) and newly developed theory-informed exercises (i.e., 3-min wake-up and friendly reminder).

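### Practice quality is to be tested as a moderator of trajectory effects, but no workable across-day model contains it for two of the daily valued-living items, and only a nominal one does for a third

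*Protocol article*

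**What the plan says.** Hypothesis 3 (section 1.5) states that "higher quality of values practice will be associated with stronger microintervention effects referred to in Hypothesis 1 across the three temporal levels". Section 1.4.2 gives the mechanism: with stronger imagery and bodily engagement, "individuals may experience a deeper connection with their values and, consequently, greater valued living". The Discussion names a narrower aim, "whether quality of practice moderates proximal and trajectory effects".

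Section 2.11 assigns this to the mixed models: to test proximal and trajectory effects "as well as the moderating role of quality of practice (Objectives 1.a, 1.b, 2, and 3), linear mixed-effects models will be fitted". It then lists the fixed effects model by model.

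- **Birthday party:** time, quality and their interaction. For values awareness, frequency of valued actions and awareness during valued actions, the later reading is the next morning's, and models with condition are added.
- **3-min wake-up:** condition (two arms), time, day, quality and interactions.
- **Friendly reminder:** "For the friendly reminder microintervention, condition (RWM, CWM, control), time (pre- vs. post-microintervention), day (from 1 to 6), quality of practice, and their interactions".
- **First assessment of each day:** used to "examine whether values awareness, frequency of valued actions and awareness during valued actions change across repeated daily engagement with the intervention". Its terms are: "Condition (RWM, CWM, control), day (from 1 to 6), and their interaction will be entered as fixed-effect predictors".

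**The concern.** Section 1.5 defines trajectory effects as changes across days with repeated use. The three items above record whether values were noticed and acted on in daily life, which is where section 1.4.2 expects good practice to show. Section 2.11 itself accepts that they need time to respond, and uses a next-day reading for them after the birthday party. The same reasoning is not carried to the six wake-ups, although short quality items follow each one.

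If the plan is run as listed, a null or positive answer on quality and trajectories would come only from items rated before and after the exercise in one sitting with the quality rating. That shared sitting invites overlap between the two ratings. A report could then say that trajectory moderation was examined when it was not examined for the daily-action items.

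**Working it through.** No published figure is at issue. The check sets each item's measurement points against each model's terms.

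**Step 1: where the items are rated (Table 2).**

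| Item | Wake-up, before | Wake-up, after | Reminder, before |
|---|---|---|---|
| Values awareness | yes | no | yes |
| Frequency of valued actions | yes | no | no |
| Awareness during valued actions | yes | no | no |

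The reminder has no column for a rating afterwards. No quality item is marked at the reminder.

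**Step 2: which models have both day and quality.** Only the wake-up and reminder models do.

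- The wake-up model contrasts before with after. None of the three items has an after-rating, so none fits.
- The reminder model can hold values awareness only, through "Since the last notification, to what extent have you been aware of your values? (for friendly reminders notifications". For that item time has a single level, no quality rating is taken at the reminder, and the control arm, which answers only the pre-questions (section 2.6), has no quality score at all.
- The birthday-party models have quality but cover one interval after one exercise, so they say nothing about change across days.
- The first-assessment model has day but not quality.

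**Step 3: result by item.**

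| Item | Across-day quality test | Next-day quality test after birthday party |
|---|---|---|
| Values awareness | nominal only | plausible, text ambiguous |
| Frequency of valued actions | none workable | plausible, text ambiguous |
| Awareness during valued actions | none workable | plausible, text ambiguous |

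**Step 4: could quality simply be added to the three-arm model?** Inputs: 159 participants (section 2.2) at 1:1:1, so 159 / 3 = 53 per arm, and 6 days. Planned rows: 159 x 6 = 954. Rows that can carry a quality score (RWM and CWM): 106 x 6 = 636. The design for condition (three levels) by day (linear) by quality has 3 x 4 = 12 columns. On the rows with quality its rank is 8, because the four control columns are empty. The control terms cannot be estimated, so a separate two-arm model is needed.

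**Step 5: data available for such a model.** Six wake-ups give 5 pairs of one day's quality with the next morning's rating. At full compliance this is 106 x 5 = 530 pairs, and within-person degrees of freedom are about 530 - 106 = 424. With 80% power and two-sided 5%, the detectable within-person correlation is about 2.8 / sqrt(424) = 0.136, or roughly 0.14. This is for a lagged main effect with every rating present. It does not size a quality by day interaction.

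**Step 6: time order.** These items look back 24 hours (the reminder version looks back to the last notification), and the wake-up is open from 6:00 a.m. to 12:00 p.m. (section 2.7). Practice at noon followed by a rating at 6:00 a.m. leaves 18 hours after the practice, so up to 24 - 18 = 6 hours of the recall window come before it. Quality mostly, but not wholly, precedes the outcome period.

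**The case against.** Several points on the other side have force.

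- **The first-assessment model has its own purpose.** It compares all three arms over days for Hypotheses 1 and 2, and control has no quality score. Leaving quality out of that model is right. What stands as a gap is that no companion model takes its place.
- **A reader might infer that Hypothesis 3 is wholly untested for these items.** The document does not support that. The birthday-party paragraph enters quality and its interaction with time, then moves these items to the next-day reading and adds condition. Nothing says quality is removed.
- **A reader might infer that the first-assessment model is the only across-day model for all three items.** For values awareness that is not so, since the reminder model lists day and quality. Its cover is nominal for the reasons in Step 2, but it is on the page.
- **The Discussion does not promise the test for every item.** The wake-up model does contain quality by day terms for ten items: eight on mental health, plus values clarity and intention. Yet Hypothesis 3 refers to the effects in Hypothesis 1, which include the values-related outcomes without exception.
- **Objective 3 is exploratory, and an article may leave detail to a fuller plan.** That limits the weight of the point. It does not remove it, because section 2.11 states the terms of each model and the stated terms do not meet the stated hypothesis.

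**Conclusion.** The point holds at the trajectory level. For frequency of valued actions and awareness during valued actions, two of the five momentary valued-living processes, no model that fits the measurement schedule has both day and quality. For values awareness there is one such model on paper, and it cannot be fitted as written. No conclusion is drawn about the proximal level, where the birthday-party next-day analysis may already do the work.

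This rests on reading Table 2 and the lists of fixed effects as complete. The design figures assume 53 per arm, and the pair count and detectable correlation also assume full compliance. The Discussion expects attrition, so the usable pairs will be fewer and the detectable correlation larger. Because the moderator is exploratory, this is a modest improvement to the analysis and no threat to the three-arm comparison.

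**What to change.** 1. Keep the three-arm condition by day model without quality for Hypotheses 1 and 2.
2. Add, in RWM and CWM only and labelled exploratory, one mixed model for each of the three next-morning items, with participant as a random effect. Predictors: the previous day's wake-up quality (centred on the person's mean), the person's mean quality, condition, day, and quality by day, with condition interactions if wanted. The quality by day term is needed. A lagged main effect alone relates quality to the level of the outcome and does not test whether the trajectory differs.
3. State that quality and its interaction with time stay in the birthday-party next-day models once condition is added. This links the day-1 quality score to the first morning reading.
4. If these models are not wanted, narrow Hypothesis 3 and the Discussion sentence to the outcomes for which quality is actually tested.

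The cost is three more exploratory models on data already collected, with somewhat more multiplicity to report. The write-up should note that the 24-hour recall window can partly precede the previous day's practice.
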